**Figure 1 F1:**
[figure not shown]
Study diagram. BREM, benefits of real-ear measurements; HA, hearing aid; ISO, International Organization for Standardization; KUH, Kuopio University Hospital.

### Participants

Up to 200 older adults (65–84 years of age) with mild to moderately severe sensorineural hearing loss^1^ are recruited from October 2024 onwards at the KUH among patients referred to the ENT clinic for HA rehabilitation of sensorineural hearing loss. Patients with conductive or asymmetrical hearing loss, HA contraindications, diagnosed cognitive impairment or cognitive concern under evaluation or any health condition affecting their ability to participate in the study are excluded. The eligibility criteria for the trial are presented in table 1. Patients are first screened as part of their routine hearing loss assessment appointment by an ENT specialist, and eligible patients are invited to participate in the study. A study nurse will obtain informed consent from the participants during the same appointment (online supplemental material S2). The recruitment for this study started on 1 October 2024, and the anticipated primary completion date is estimated to be 29 February 2028.

**Table 1 T1:** Eligibility criteria

Inclusion criteria	Exclusion criteria
Age 65–84 years	Conductive hearing impairment (air-bone gap>20 dB HL in two consecutive frequencies)
Mild to moderately severe sensorineural hearing loss, pure-tone average (0.5–4 kHz) between 20 and 64 dB*	Difference between the hearing levels of the ears is >15 dB HL in three consecutive frequencies
Community-dwelling, that is, living at home/not living in a care home or nursing home	HA contraindication
Proficiency in Finnish language	Cognitive status: Previously diagnosed dementia or current use of cholinesterase inhibitors and/or memantine. If there is a current ongoing diagnostic process for suspected dementia, the decision on eligibility will be made by an experienced study physician based on medical records and clinical judgement.
First-time HA user	Any health conditions severely impairing vision (no predefined visual acuity threshold), mobility, communication or ability to participate in study visits and complete study assessments, as judged by the study nurse and/or physician.

* As per the Global Burden of Disease Expert Group on hearing loss criteria.

dB HL, decibel hearing level; HA, hearing aid.

### Patient and public involvement

Patients and/or the public were not involved in the design, conduct, reporting or dissemination plans of this research. Patients will be recruited only as study participants.

### Data collection

Eligible participants (table 1) are undergoing baseline assessments prior to randomisation. The same outcome assessments will be repeated at 12-month and 24-month follow-up visits after the beginning of the intervention, which is defined by the date of the first HA fitting appointment. Table 2 and online supplemental material S3 summarise the time schedule of the HAHA assessments. All outcome assessments are performed by study nurses specifically trained in the HAHA study procedures, who are masked to participants’ group allocation.

**Table 2 T2:** Schedule of enrolment, interventions and assessments of the HAHA trial

	Study period						
	Pre-enrolment	Enrolment baseline assessment and allocation*	Post-allocation				Close-out
TIMEPOINT**	Screening	Baseline	Primary fitting visit (t_0_)	3 M	6 M	12 M	24 M
ENROLMENT:							
Eligibility screening†	X						
Informed consent		X					
Allocation		X					
INTERVENTIONS:							
DDHR intervention							
Standard care							
Primary HA fitting (all participants)			X				
Re-fitting DDHR				X‡	X‡	X‡	X‡
Standard care follow-up phone call				X			
Standard care possible additional visits§							
ASSESSMENTS:							
Screening and baseline variables¶	X	X					
Outcomes variables**		X				X	X
REAR measures††			X				

* Enrolment will take place after the screening assessment that is conducted as part of the standard ENT clinical and diagnostic work-up; to prevent allocation affecting the baseline assessments, the primary outcome assessments will be conducted before allocation. The intervention will start as soon as possible after allocation, based on the timeline for HA fitting as part of the standard clinical management of the patients.

† The screening assessment is conducted prior to enrolment as part of the standard ENT clinical and diagnostic work-up.

‡ As needed based on participant feedback, the DIN test results and/or clinical judgement.

§ As needed based on participant request.

¶ For the full list of assessments, see the ‘Eligibility’ and ‘General Covariates’ sections of the Supplementary material S3.

** For the full list of assessments see ‘General Covariates’; ‘Medical History’; ‘Anthropometrics’; ‘Primary Outcomes’; ‘Secondary Outcomes’; ‘Cognitive Measures’; ‘Quality of life and other psycho-social measures’; ‘Exploratory/Optional Assessments’; ‘Vision-related measures’ and ‘Blood samples’ sections of the Supplementary material 3.

†† DDHR group.

DDHR, data-driven hearing rehabilitation; DIN, digits-in-noise; ENT, ear, nose and throat; HA, hearing aid; 3 M, 6 M, 12 M and 24 M, 3, 6, 12 and 24 months from primary fitting visit (t_0_); REAR, real-ear aided response.

#### Primary outcomes

Change in SPIN will be assessed with two tests/outcome measures: the Finnish matrix sentence test (FMST)^19^ and digits-in-noise (DIN) test.^20
21^

FMST is a functional audiological test validated for the Finnish language.^19^ In the test, participants listen to 5-word sentences chosen from a standardised and optimised word matrix, which allows for 105 different sentences of equal intelligibility. Each test list contains 20 randomly chosen sentences. The sentences are presented to the participants under stationary background noise (65 dB SPL) generated from the speech material of the FMST. The test is presented in the S0N0 condition, which means that the signal and background noise are presented through one loudspeaker at a 0° azimuth. Three test lists will be presented to the participants. The participants repeat all the words they can identify, and they are allowed also to guess words that they could not hear clearly. The result of the FMST is the signal-to-noise ratio (SNR) at which the participant correctly identifies 50% of the presented word items; this is called the speech reception threshold (SRT50).DIN is a functional hearing test^20^ validated for the Finnish language.^21^ The word material of the test consists of digit triplets presented under stationary background noise (65 dB SPL). The result of DIN is the SNR at which the participant correctly identifies 50% of the presented triplets (SRT50). The DIN will be performed as a closed-set test, which means that the participant types their responses via a touch screen. Participants will be tested during the baseline visit without HAs and during the following visits (12 and 24 months) with and without HAs in both ears simultaneously.

#### Secondary outcomes

Changes in the following secondary endpoints will be included: Hearing in Real-Life Environment (HERE)^22^ and Speech, Spatial and Qualities of Hearing Scale (SSQ)^23^; HA usage, self-report and HAs log-data; listening effort questionnaire^24^; response time of the DIN test and tinnitus handicap inventory (THI)^25^; Consortium to Establish a Registry for Alzheimer’s Disease -test’s (CERAD-nb) global and domain scores^26^; Clinical Dementia Rating Sum of Boxes^27^; health-related quality of life (15D and EQ5-D-5L questionnaires^28
29^); self-reported depression symptoms and Beck Depression Inventory^30^ (table 2, online supplemental materials S3 and S4).

#### Exploratory outcomes

A range of exploratory analyses will investigate potential intervention effects on active lifestyle (change in lifestyle factors related to cognitive decline, eg, physical, cognitive and social activities) as well as accessible and non-invasive biomarkers as possible predictors of hearing rehabilitation benefits. These biomarkers include electroencephalogram (EEG)-derived CAEPs, in which the analysis focuses on the amplitude, latency and duration of the sustained potential of the speech-evoked response and brain structural MRIs probing the effects of hearing impairment and rehabilitation on volumetric measures. The full list of exploratory outcome measures is presented in online supplemental material S3.

#### Other data collected

Other relevant data will be collected, including demographics, medical history, anthropometrics, subjective memory questionnaire,^31^ Basic Nordic Sleeping Questionnaire^32^ and other lifestyle-related risk factors for cognitive decline (eg, diet, smoking and alcohol consumption). Audiograms will be obtained through pure-tone audiometry using an Aurical Aud audiometer (Natus Medical Incorporated, Middleton, WI, US) with TDH39 audiometric headphones (TTM Technologies Inc., St. Louis, MO, US) in a soundproof booth, following international standards (ISO 8253–1:2010). Air conduction (AC: 250–8000 Hz) and bone conduction (BC: 250–4000 Hz) measurements are performed by experienced audiometricians. The pure-tone average is calculated for AC (mean of 500, 1000, 2000 and 4000 Hz). Vision-related measures (ie, best-corrected visual acuity, slit-lamp examination, retinal imaging, eye geometrics and biometrics values) are collected to investigate the impact of dual (hearing and vision) sensory impairment on cognition. At baseline and 24 months, non-fasting venous blood samples will be collected from all participants and stored for future measurements of biomarkers for diseases related to cognitive decline (eg, genetics related to amyloid, τ, neurodegeneration or other future relevant biomarkers).

#### Safety reporting

HAs are safe and well tolerated, with no known serious health risks. Pre-specified adverse events (eg, ear canal infection, skin conditions) and serious adverse events will be monitored throughout the trial by an independent Data and Safety Monitoring Board.

### Study intervention

Participants in the DDHR intervention group will receive data-driven and regularly controlled HA rehabilitation that is not part of the standard care protocol. Prescription HAs with custom earmoulds will be fitted by using REM in accordance with the recommendations of the latest ISO standard (21388:2020) and a recent review article on the best practices for HA fitting.^33^ In addition, preliminary unpublished findings from the benefits of REM (BREM) study (ClinicalTrials.gov identifier: NCT05621798) suggest that REM-based fitting may result in improved SPIN performance compared with conventional fitting methods. The fittings are conducted by audiometricians specifically trained in the DDHR programme procedures. The gain of sound amplification is set to 100%. After the fitting of the HAs, participants’ auditory-related outcomes will be assessed at the 3-, 6- and 12-month follow-up visits using the DIN test. If needed, re-fitting will be performed based on the following criteria derived from the preliminary data of the BREM study:

The absolute improvement in the DIN<1.5 dB (SNR), ORThe absolute result of the DIN test>than −8.5 dB (SNR), ORThe participant is unsatisfied with the HA fitting.

If re-fitting is needed, the log-data of the HAs will be verified, and the following procedures will be performed based on the audiometrician’s clinical experience:

Overall usage <6 hour/day: The reason for low usage is probed, and the participant is encouraged to use the HA more. If the amplification of the HA is reported to be too loud, the sound amplification gain can be lowered to 90%. Fine-tuning of specific frequencies is also allowed based on the participants’ feedback.Overall usage ≥6 hour/day: The participant’s satisfaction with ongoing HA rehabilitation is inquired. If the participant is satisfied, no further adjustments are needed. If the participant is unsatisfied, the audiometrician is allowed to change the sound amplification gain between 90% and 110% or perform fine-tuning of specific frequencies depending on the participant’s feedback.

### Control group

The participants in the control group will receive standard care HA rehabilitation currently conducted at the KUH ENT clinic. Prescription HAs with custom earmoulds will be fitted using the manufacturers’ proprietary fitting algorithms and REM fitting will be performed only in complex cases, based on the clinical judgement of the audiometrician. In the control group, HA fittings are performed by audiometricians following routine clinical practice and who have not received specific training in the HAHA study procedures. Three months after the HA fitting, participants will be contacted via telephone and asked about the status of the rehabilitation. Additional monitoring visits may be offered based on participant feedback. Individual HA settings will be decided by the audiometrician based on clinical judgement and without predefined sound amplification gain levels. Further adjustments will be made only on a participant’s request. Due to the possible variability of the fitting procedures, the key rehabilitation process variables will be documented (eg, fitting verification method, number of follow-ups, types of adjustments and HA usage data) and reported descriptively.

### Statistics

Power calculations were based on the primary comparison, that is, the 12-month SPIN change measured using FMST and DIN in the standard care (control) versus DDHR (intervention) group. To our knowledge, no data were available on the effects of HA rehabilitation on performance in the Finnish-language SPIN tests. We assumed a 12-month mean (SD) SPIN change of −0.9 (1.2) dB in the control group, based on preliminary data from the KUH ENT clinic.^34^ We also assumed a 12-month mean (SD) SPIN change of −2 (2.5) dB in the intervention group, based on published data on HA acclimatisation in older adults under conditions comparable to the HAHA intervention (10). To show a between-group difference with 90% power and at a 2.5% significance level (Bonferroni correction for two primary outcomes), with a 10% drop-out rate during 12 months, a n=180 (90/group) sample size would be needed. The HAHA trial will recruit up to 200 participants to maintain power during the 12-month extended follow-up (assuming 20% drop-out for 2 years).

Mixed-effects regression models will be applied to analyse change in each of the primary outcomes (FMST and DIN tests) as a function of randomisation group, time (continuous in days from baseline) and group×time interaction. Short-term intervention effects will be analysed based on data from the baseline (without HA) and 12-month (with HA) visits. Long-term intervention effects will be analysed based on data from baseline (without HA), 12-month (with HA) and 24-month (with HA) visits. Non-linearity of change will be considered in the analysis of the long-term intervention effects.

Statistical significance will be evaluated using the Hochberg method to account for the two primary outcomes. Secondary outcomes will also be analysed using the appropriate generalised mixed-effects regression model, depending on the distribution of the outcome.

Analyses of auditory outcome measures will include both short- and long-term intervention effects as follows:

Change in HERE, SSQ, listening effort questionnaire, response time and THI will be analysed as a function of randomisation group, time (continuous in days from baseline) and group×time interaction. Data from baseline and 12-month visits will be used to analyse short-term intervention effects, and data from baseline, 12- and 24-month visits will be used for longer-term effects.Change in HA usage will be analysed as a function of randomisation group, time (continuous in days from primary HA fitting) and group×time interaction. Data from the 3- and 12 month visits will be used to analyse short-term intervention effects, and data from the 3-, 12- and 24-month visits will be used for longer-term effects.

Analyses of cognitive outcomes, where a longer time is needed to observe significant change compared with auditory outcomes, will focus mainly on the longer-term effects, analysed based on data from baseline and 12- and 24-month visits.

Analyses of quality of life and other psychosocial outcome measures will include both short-term (baseline and 12months) and longer-term (baseline, 12- and 24 months) intervention effects. Additional information on sensitivity analyses, accounting for missing or spurious data, and reporting dropouts is presented in online supplemental material S5.

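### The primary model leaves each arm its own baseline mean, so it essentially compares raw change and gives up precision that the pre-randomisation speech-in-noise score could supply

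*Protocol article*

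**What the plan says.** The Statistics section of the protocol article states: "Mixed-effects regression models will be applied to analyse change in each of the primary outcomes (FMST and DIN tests", each modelled on randomisation group, time in days from baseline, and group×time. For the primary time point, "Short-term intervention effects will be analysed based on data from the baseline (without HA) and 12-month (with HA) visits". The speech-in-noise (SPIN) result is the signal-to-noise ratio at 50% correct, the speech reception threshold (SRT).

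Under Data collection, eligible participants "are undergoing baseline assessments prior to randomisation", and the first footnote to Table 2 confirms that the primary outcome is assessed before allocation. Table 1 requires a "pure-tone average (0.5–4 kHz) between 20 and 64 dB", so pure-tone average is also known for everyone at entry. Randomisation is in blocks of four, and no stratification factor is named.

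The sample size is built on unadjusted change: "We assumed a 12-month mean (SD) SPIN change of −0.9 (1.2) dB in the control group" and "We also assumed a 12-month mean (SD) SPIN change of −2 (2.5) dB in the intervention group", "with 90% power and at a 2.5% significance level (Bonferroni correction for two primary outcomes" and 10% drop-out, giving 180 participants (90 per group).

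The same three-term structure is then set for several secondary outcomes that have a baseline value, including HERE, SSQ, listening effort, response time and THI.

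**The concern.** In a model with group, time and group×time, the group term is the arm difference at baseline. Randomisation after the baseline test makes that difference zero in expectation, yet the model estimates it freely. With two visits this fixes the weight on the baseline score at 1. When the true regression of follow-up on baseline has a slope below 1, whatever imbalance occurs by chance is over-corrected, and the interval is wider than it needs to be.

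What is at stake is precision in the primary comparison. It matters somewhat more here because the article says that no data were available on the effect of hearing-aid rehabilitation on the Finnish-language SPIN tests, so the planning effect is uncertain and spare precision has value.

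**Working it through.** **1. The plan's own figure.** Inputs from the Statistics section: mean changes −0.9 and −2 dB (difference 1.1 dB), SDs of change 1.2 and 2.5 dB, α = 0.025 (taken as two-sided), power 90%, drop-out 10%.

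- Average change variance: (1.2² + 2.5²)/2 = (1.44 + 6.25)/2 = 3.845, root 1.961 dB.
- Normal approximation: n = 2(2.241 + 1.282)² × 3.845/1.1² ≈ 79 per arm; 79/0.9 gives 88 per arm.
- t-based (Welch): 81 per arm, power 90.1%; 81/0.9 = 90 per arm, 180 in all.

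The stated 180 is reproduced from raw change, with no adjustment.

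**2. Is the stated model a change-score comparison?** One simulated complete two-visit data set, 81 per arm:

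| Analysis | Estimate | SE |
|---|---|---|
| Group, time, group×time (as stated) | −0.713 | 0.251 |
| Difference in mean change | −0.713 | 0.251 |
| ANCOVA on baseline | −0.764 | 0.227 |
| Stated model + pure-tone main effect | −0.713 | 0.251 |
| Stated model + pure-tone × time | −0.752 | 0.239 |

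The first two rows agree. A pure-tone main effect leaves the interaction SE unchanged, because it shifts both visits equally; only a time interaction reduces it. The simulation settings were invented, so the table shows which analyses coincide, not how large the gain in this trial will be.

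**3. Size of the gain.** In general, conditioning on baseline multiplies the variance of the change contrast by 1 − r², where r is the correlation of baseline with change. The documents give neither r, nor the baseline to 12-month correlation ρ, nor the baseline SD. Assume equal SD σ at both visits:

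- change: 2σ²(1 − ρ)
- ANCOVA: σ²(1 − ρ²)
- ratio: (1 + ρ)/2

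The planned SDs imply a different ρ in each arm, since (1 − ρ_DDHR)/(1 − ρ_control) = 6.25/1.44 = 4.34. With equal arms and a common slope equal to the average ρ, the averaged residual variance is still σ²(1 − ρ²), so the ratio holds with ρ read as the between-arm average. An average of 0.5, for example, corresponds to about 0.81 in control and 0.19 in DDHR.

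| Average ρ | Variance ratio | Reduction | Power, 81 per arm (Welch) |
|---|---|---|---|
| no adjustment | 1.00 | – | 90.1% |
| 0.5 | 0.75 | 25% | 96.7% |
| 0.7 | 0.85 | 15% | 94.4% |
| 0.8 | 0.90 | 10% | 93.1% |

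Without the equal-SD assumption, the reduction is 0% for r = 0, 1 − 0.91 = 9% for |r| = 0.3, and 25% for |r| = 0.5.

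**The case against.** **No error is shown.** Randomisation makes the stated contrast unbiased, chance imbalance is already reflected in its standard error, and 180 was sized on unadjusted change. All of this stands. A reader might infer that the trial is biased or underpowered; the article's figures show neither.

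**The equivalence is not exact.** Time is counted in days from baseline, while the 12-month visit is counted from first fitting, which follows a 3–6 month wait, so intervals vary between participants. Under drop-out, a mixed model also keeps people who have only a baseline score. This stands, hence the word essentially. It does not remove the free baseline mean.

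**The article is condensed.** Supplement S3 has a section on general covariates and S5 holds further analysis detail; neither is shown. It therefore cannot be said that pure-tone average will go unadjusted. But the group term is stated in the article itself, and covariates entered as main effects would not undo it.

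**The gain is assumed.** Baseline is unaided and follow-up aided, so equal SDs are doubtful, and the gain may be nil. This stands, which is why a range is given.

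**Unequal variances.** A reader might infer from SDs of 1.2 and 2.5 dB that a common-variance test inflates type I error. With 72 DDHR and 90 control completers, the nominal 2.5% becomes about 3.7%. That needs 20% drop-out in one arm and none in the other, which nothing in the article suggests. At 81 per arm the error is about 2.5%, and with the imbalance reversed about 1.6%. The article states no covariance structure at all, which is ordinary analysis-plan detail. This is not a finding.

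**Conclusion.** The point holds as one of efficiency. The primary model, as the article fixes it, estimates a baseline difference that the design sets to zero, and so works essentially on raw change. Conditioning on baseline SPIN is never less precise in large samples. Under equal SDs and an average ρ of 0.5 to 0.8, the variance falls by 25% to 10% and power at 81 per arm goes from 90% to about 97% to 93%. These figures rest on an assumed ρ, and the lower limit is no gain. Validity and the planned power are not in question. Any further gain from pure-tone average beyond baseline SPIN is unknown.

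**What to change.** State one of these as the primary analysis for FMST and DIN:

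- a longitudinal model with a baseline mean common to both arms, visit as a factor, and visit×group terms from 12 months on; or
- ANCOVA of the 12-month aided SRT on the baseline unaided SRT.

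Use the same form for secondary outcomes with a baseline value. If pure-tone average is added, enter it in the ANCOVA or with a time interaction, and name the covariates and their form in advance.

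The cost is a change of wording in the protocol or analysis plan before unmasking. No extra data, visits or participants are needed, and the sample size can stay as it is. Primary completion is expected in February 2028, so there is time to prespecify it.

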## Methods and analysis

### Study design

HAHA is a proof-of-concept, single-site, two-arm parallel group, 12-month RCT with a 12-month extended follow-up (figure 1). Eligible participants are randomly allocated 1:1 to either the DDHR programme (active group) or the standard care (control group). In this study, ‘data-driven hearing rehabilitation’ refers to a structured, clinician-led fitting approach in which established verification procedures are used to ensure accurate amplification, combined with the systematic use of objective outcome measures (eg, SPIN performance, HA usage data and PROMs) to guide rehabilitation decisions according to predefined criteria. This approach is clinician-implemented and does not involve algorithmic or artificial intelligence-based decision-making. Standard care corresponds to the routine hearing rehabilitation programme currently provided at the Kuopio University Hospital (KUH) ENT clinic. HAs will be fitted using the manufacturers’ proprietary fitting algorithms, and real-ear measurements (REM) will be performed only in complex cases, based on the clinical judgement of the audiometrician. The main difference is that routine standard care does not typically include systematic assessment of rehabilitation outcomes, which may contribute to suboptimal outcomes and reduced adherence to HA use. To ensure a balanced distribution between the groups, randomisation is performed using a computer-generated list in blocks of four and with sealed envelopes. The list and the envelopes are prepared by a biostatistician and used by a study nurse to randomise the participants. Although double-masking is not possible, outcome assessors will be masked to the group allocation. Participants will not be actively informed of their group allocation; however, complete masking may not be feasible based on differences between the HA fitting protocols. The HAHA trial is completely embedded in clinical practice, and all trial participants will receive the same HAs as in routine care. Due to its pragmatic approach, the HAHA trial will follow the standard care wait-time (3–6 months) for the primary HA fitting visit, which marks the beginning of the intervention. Analyses will follow CONSORT guidelines^16^ and will include the intention-to-treat population, that is, all randomised participants, except for those who withdraw their consent (including for use of data). The Standard Protocol Items: Recommendations for Interventional Trials checklist^17

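### The primary model tests a per-day slope from enrolment, not the between-arm difference in change at the visit 12 months after fitting on which the trial was powered

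*Protocol article*

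**What the plan says.** The Statistics section of the protocol article models FMST and DIN "as a function of randomisation group, time (continuous in days from baseline) and group×time interaction". The short-term analysis uses the unaided baseline and the aided 12-month visit. Non-linearity is mentioned only for the long-term analysis, which adds the 24-month visit.

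The calendar is set elsewhere. Under Study design, "the HAHA trial will follow the standard care wait-time (3–6 months) for the primary HA fitting visit", and that visit starts the intervention. Under Data collection, baseline assessments come before randomisation, and the 12- and 24-month visits are timed from the start of the intervention, "which is defined by the date of the first HA fitting appointment". The key to Table 2 confirms that the month labels count from the primary fitting visit.

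The power statement concerns "the 12-month SPIN change measured using FMST and DIN in the standard care (control) versus DDHR (intervention) group".

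**The concern.** The model's clock starts at the unaided enrolment assessment, while the visit calendar starts at fitting. On the model's clock the visit labelled 12 months falls about 15–18 months out, and the first 3–6 of those months pass without hearing aids in either arm. The short-term analysis has two time points and no non-linear term, so continuous time amounts to a straight line. The interaction is then a difference in dB per day over an interval that includes the wait.

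Two things are at stake. First, the tested coefficient is not the quantity that was powered, and a reader who converts it to 12 months in the obvious way gets too small a number. Second, the wait arises after allocation. The two arms are fitted by different audiometricians: specially trained in the data-driven arm (DDHR), routine staff without study-specific training in the control arm. If waits came to differ by arm, equal benefit would give unequal slopes.

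**Working it through.** **Inputs.** From Statistics: "We assumed a 12-month mean (SD) SPIN change of −0.9 (1.2) dB in the control group" and a "12-month mean (SD) SPIN change of −2 (2.5) dB in the intervention group", so a difference of 1.1 dB; 90% power; 2.5% significance per outcome; 10% drop-out; 180 participants (90 per group). From Study design: a wait of 3–6 months. From Data collection and Table 2: visits timed from fitting.

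**1. The plan's sample size.** Taking the 2.5% as two-sided:

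n per arm = (1.2² + 2.5²)(2.2414 + 1.2816)² / 1.1² = 7.69 × 12.41 / 1.21 = 78.9, so 79.

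With the Welch t distribution, 81 per arm gives 90.1% power, and 81/0.9 = 90 per arm, or 180 in total. The plan's figure reproduces, and it is a calculation for a difference in mean change.

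**2. What the interaction estimates.** If the true difference at the aided visit is 1.1 dB and the wait is w months, the slope difference is 1.1/(12 + w) dB per month. Read at 12 months on the model's clock, that is 1.1 × 12/(12 + w):

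| Wait | Visit on the model's clock | Slope read at 12 months | Shortfall from 1.1 dB |
|---|---|---|---|
| 3 months | 15 months | 0.88 dB | 20% |
| 4.5 months | 16.5 months | 0.80 dB | 27% |
| 6 months | 18 months | 0.73 dB | 33% |

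Multiplied by the actual time of the visit, the slope returns 1.1 dB. With waits spread over 3–6 months in both arms, simulation gives 0.80 dB at 12 months from baseline and 1.10 dB at the mean visit time.

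**3. Dependence on the wait.** Two participants who each change by −2 dB, one after a 3-month and one after a 6-month wait, have 12-month slopes of −2 × 12/15 = −1.60 dB and −2 × 12/18 = −1.33 dB. They differ by 0.27 dB with no difference in benefit.

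**4. Effect on the test.** Simulation with 81 completers per arm, SDs of change 1.2 and 2.5 dB, two time points, and change independent of the wait. The model was fitted with a random intercept (assumed baseline SD 2.5 dB) and, as a check, on within-person changes. Ranges span repeat runs. The waits by arm are assumptions, because the article gives none.

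| Waits (control / DDHR, months) | Power at −0.9 v −2 dB | Null rejection, both arms −2 dB (nominal 2.5%) |
|---|---|---|
| 3–6 / 3–6 | about 90% | about 2.5% |
| 3–5 / 4–6 | 85% | 3.2–3.5% |
| 3–4 / 5–6 | 77–78% | 6.4–6.9%, nearly all favouring control |
| 5–6 / 3–4 | 96% | 8.2–8.4%, nearly all favouring DDHR |

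At a common change of −0.9 dB, the 3–4 / 5–6 split gives only 2.7–3.4%. With visit as a factor, power stays near 90% and null rejection at 2.4–2.9% in every scenario.

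**The case against.** The article never says that the slope will be read at day 365. With two visits, scaling to the actual visit time recovers the planned contrast, and with similar waits the test behaves as designed. The article gives one wait for the whole trial, tied to routine clinical scheduling, and nowhere says that waits differ by arm. All of this stands. It limits the point to the estimand plus a conditional risk to the test. The 3–4 v 5–6 month split is deliberately extreme, and the bias can run either way.

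The reporting scale of the interaction could be settled in an unseen analysis plan or in supplement S5. But the published text does not leave the time scale open: it fixes one that does not match the powered comparison.

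A reader might infer four stronger points that the documents do not support:

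- *That the sample size or power is wrong.* N=180 reproduces, and power is unchanged when waits are similar.
- *That the plan contradicts itself because hearing-aid use is modelled with "time (continuous in days from primary HA fitting").* Use cannot precede fitting, so that origin is natural there. SPIN has a pre-fitting baseline, so counting from baseline is a choice, not a contradiction.
- *That the long-term model will force a line through one unaided and two aided visits.* The article says non-linearity will be considered in exactly that analysis.
- *That benefit is a pure step at fitting.* The Introduction describes gradual acclimatisation. The point does not need a step; it needs only that the wait without aids counts in the interval.

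**Conclusion.** The point holds as a mismatch between the primary model's coefficient and the powered comparison, and it should be fixed. The coefficient is a per-day slope over about 15–18 months, in which each participant's change is spread over a wait that arises after allocation. The 20–33% shortfall arises only if the slope is read at 12 months from baseline. Power, type I error and N are sound if waits are similar in both arms.

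Harm to the test requires waits that differ by arm. Separate fitting staff make that possible, but the document gives no evidence of it. Under the assumed splits above, power ranges from about 77% to 96%, and null rejection at a common −2 dB change reaches about 7–8%. The excess favours whichever arm waits less. These figures also assume that change at the aided visit does not depend on the wait.

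**What to change.** For FMST and DIN:

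- Treat time as a categorical visit (baseline, 12 months, 24 months).
- Define the primary effect as the between-arm difference in change from the unaided baseline to the aided visit 12 months after fitting.
- Take the 24-month contrast from the three-visit model.
- Report the baseline-to-fitting wait by arm, and use it at most in a sensitivity analysis.

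Apply the same visit coding to the other auditory outcomes now modelled in days from baseline: HERE, SSQ, listening effort, DIN response time and THI. Moving the origin to fitting while keeping a straight line would not cure the problem, because the interval between the two measurements would still be 12 months plus the wait.

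The cost is wording in the protocol and analysis plan. No extra data are needed, and N and planned power stay as they are. With primary completion anticipated for February 2028, the change can be made before results are known.
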